## Abstract

**Background:**

With advancing age among older adults, the associated debilities increase, indicating a deteriorating health status as there is a gradual loss of muscle mass, strength, and functionality. *Ayush Rasayana* A and B are coded Ayurvedic medicines developed from herbal extracts. This study has been planned to prevent debilitating conditions and improve the quality of life (QOL) in older adults.

**Objective:**

This study aimed to assess the effectiveness of *Ayush Rasayana* A and B on the QOL, quality of sleep, and functionality of older adults, along with the tolerability of the intervention.

**Methods:**

This was a multicenter, open-label, cluster randomized controlled trial conducted with 720 participants aged 60 to 75 years. The participants were divided into 2 groups (intervention and control), with both receiving Ayurvedic ancillary treatment for 3 months. The intervention group additionally received 10 g of *Ayush Rasayana* A orally once daily at bedtime for 6 days, followed by 1.5 g of *Ayush Rasayana* B orally twice daily before food for the remaining 84 days. The assessment criteria included the Older People’s Quality of Life Questionnaire Brief, Katz Index of Independence in Activities of Daily Living, Pittsburgh Sleep Quality Index, Five Times Sit-to-Stand Test, and shoulder and scapular movements. Any change in hematological and biochemical parameters and occurrence of treatment-emergent adverse events were also assessed during the study period.

**Results:**

The recruitment of the participants started in December 2023, and the final follow-up was completed in April 2024. Out of the total 720 enrolled participants, 686 (95.3%) completed the study up to the last follow-up.

**Conclusions:**

This study may provide evidence-based data to establish preventive treatment protocols for enhancing the QOL and functionality among older adults. The study results may also be helpful for the planning of interdisciplinary health policies for improving the health conditions of different populations

**International Registered Report Identifier (IRRID):**

DERR1-10.2196/58186

## Introduction

### Background

The aging population in India is a major concern across social, political, and economic spheres. The older adult population in India is growing 3 times faster than the general population, which is attributed to the increased life expectancy [1]. A total of 27.72% of the older adult population reported having a medical condition, either short term or chronic [2]. With advancing age, there is a gradual loss of muscle mass, strength, and functionality. Studies show that chronic morbid conditions such as musculoskeletal disorders impact the quality of life (QOL) in multiple dimensions [3]. The prevalence of age-related diseases is on an upward trend, and its management is limited at this age owing to less reciprocation and multiple underlying disorders [4]. In addition to causing symptoms of structural and functional deficiencies, these age-related illnesses cause a reduction in the older adults’ total functional ability and a variety of limitations. The aging process is brought about by the damage inflicted on biological macromolecules, which act as endogenous damaging agents, creating a state of oxidative stress. This accumulated damage in cells over time leads to the loss of function or functional impairments in the body [5]. Reduced quality of sleep and increased prevalence of sleep disorders are common in advanced age. Studies show that older people have low sleep quality, and it is often associated with a lower QOL [6]. Aging is inevitable, and there is an urgent need to find interventions that help reduce the incidence of debilitating age-related diseases and promote QOL.

Ayurveda endures as a traditional and extensive discipline of traditional Indian medicine used to promote health, prevent illness, and treat physical ailments via *Jarachikitsa* or *Rasayana*. The medicines, food products, and lifestyle-related factors that enhance the quality and longevity of life have been termed *Rasayana* [7]. It is a rejuvenation therapy that has been said to impede the aging process (*Vayasthapanam*), lengthen life expectancy (*Ayushkaram*), improve intelligence (*Medha*), build strength (*Bala*), and prevent disease development [8]. According to various studies, the *Rasayana* drugs possess potent antioxidant activity when combined with dietary supplements and rejuvenators. It reacts negatively with oxidative stressors, which are what lead to the production of various free radicals [9,10]. The study drugs—*Ayush Rasayana* A and B—are coded Ayurvedic medicines; are developed from herbal extracts that have rejuvenating properties as per the classical Ayurveda textbooks; and are effective in improving health-related QOL, functional capacity, and cognition [11]. This study is planned as a multicenter, double-arm, cluster randomized controlled trial to assess the effectiveness of *Ayush Rasayana* A and B on the QOL of older adults in the selected populations.

### Objectives

The primary objective of the study is to assess the effectiveness of *Ayush Rasayana* A and B on the QOL of older adults. The secondary objectives include the assessment of the quality of sleep and functionality in the study population, along with the assessment of the tolerability of the intervention during the study period.

## Methods

### Study Design

The study was an open-label, multicenter, parallel-group, cluster randomized controlled trial conducted in 2 groups with an allocation ratio of 1:1.

### Study Participants

#### Inclusion Criteria

Participants aged 60 to 75 years were selected for the study from the identified Scheduled Caste (SC)– or Scheduled Tribe (ST)–dominant areas regardless of gender. They needed to be ambulatory, be clinically stable with or without medication, have a score of 5 or more in the Katz Index of Independence in Activities of Daily Living, and be willing to provide written informed consent for their participation in the study for 3 months.

#### Exclusion Criteria

Participants with blood pressure ≥160/100 mm Hg, hemoglobin A_1c_ (HbA_1c_) ≥8%, serum thyroid-stimulating hormone >10 mIU/mL with or without medication, elevated liver enzymes (aspartate transferase and/or alanine transaminase >2 times of the upper normal limit), impairment of renal function (defined as serum creatinine>upper normal limit), or BMI <23 or >30 kg/m^2^ were excluded from the study. Those who have a history of serious cardiac dysfunction or pulmonary dysfunction (patients with asthma and chronic obstructive pulmonary disease); those with cancer or chronic inflammatory conditions, including but not limited to chronic infection like tuberculosis, leprosy, HIV, and collagen vascular diseases; participants on hormone replacement therapy, steroid therapy, chemotherapy, or immunosuppressive therapy; and participants with alcohol use disorder were not enrolled. Those with a diagnosis of any severe cognitive or psychiatric illness, neurological disorders, hemorrhagic diseases, or coagulation disorders within 90 days before the screening were also excluded. Participants who were currently on any drugs that affected the cognitive or physical function, on any nutritional supplements or any Ayush or folk medicine for maintaining the QOL, or with any other condition that the investigator thought could jeopardize the study were also excluded from participation.

### Withdrawal Criteria

Study participants who developed any serious adverse events, developed any condition mentioned in the exclusion criteria during the study period, and were not compliant with the protocol or not willing to continue in the study were free to withdraw from the study. Detailed justification for withdrawal of the participant were prepared, indicating the line of further management, if required. The sponsor and ethics committee were informed within the appropriate time as per Ayush Good Clinical Practice guidelines.

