### Outcome Measures

The primary outcome measure was the change in the QOL of the older adults, assessed by Older People’s Quality of Life Questionnaire-Brief (OPQOL-BRIEF) at baseline and on the 34th day, 62nd day, and 90th day. The secondary outcome measures included any change in the Katz Index of Activities of Daily Living, Pittsburgh Sleep Quality Index (PSQI), Five Times Sit-to-Stand Test, shoulder joint mobility, hematological and biochemical parameters (complete blood count, liver function test, and renal function test), and the occurrence of treatment-emergent adverse events during the study period at the baseline and on the 90th day.

The OPQOL-Brief is a short measurement for QOL developed from the OPQOL-35 questionnaire [13]. It contains 13 questions scored from 1 (strongly agree) to 5 (strongly disagree) based on the response from the participant. The total score is calculated after reverse coding the positive items so that higher scores represent higher QOL. The Katz Index of Activities of Daily Living is a dichotomous scoring tool used for measuring independence in older adults. It measures the functional independence of a person, assessing self-care tasks under 6 domains: bathing, dressing, toileting, transferring, continence, and feeding [14]. The PSQI is a widely used scale comprising a combination of Likert-type and open-ended questions in 7 components: subjective sleep quality, sleep latency, sleep duration, sleep efficiency, sleep disturbance, use of sleep medication, and daytime dysfunction—each with scores ranging from 0 to 3. Higher PSQI scores indicate more acute sleep disturbances, thus a lower quality of sleep [15]. The Five Times Sit-to-Stand Test is a measure used to assess functional independence and mobility. It evaluates the time required to stand as rapidly as possible from a sitting posture for 5 repetitions; the shorter the time taken by the person, the better the functional condition [16]. The change in shoulder joint mobility is assessed through simple physical maneuvers for the active range of movements: active abduction, and external and internal rotations. Each maneuver is assessed separately by 3-point scales for the range of mobility (fully able=3, partially able=2, and unable=1) and pain on movement (no pain=1, some pain=2, and lots of pain=3) on both sides. A sum score for all 3 maneuvers on each side is estimated for the range of movement and pain separately.

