### Statistical Analysis

After data collection, verification of its accuracy and limits will be done. The filtered data will be utilized for additional analysis and interpretation. Categorical variables (eg, bowel movement: regular or irregular) will be reported as number (percentage), and the analysis of the pretrial-posttrial outcome will be done by a McNemar chi-square test. Continuous variables (eg, score and laboratory parameter) will be analyzed by a 2-tailed paired *t* test or Wilcoxon test as per the distribution of data in the pretrial-posttrial situation. Categorical variables will be analyzed through a chi-square test in the between-group comparison. Continuous variables will be analyzed through a 2-tailed unpaired *t* test or Mann Whitney *U* test in the between-group comparison. The assessment parameters assigned in more than 2 follow-ups will be analyzed using the r-ANOVA, Friedman test, or Cochran *Q* test. Continuous data with normal distribution will be represented as mean (SD), and data without normal distribution will be represented as median (IQR). The 5% level of significance will be used throughout the analysis. The SPSS (version 26.0l IBM Corp) software will be used to conduct the analysis.

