## Results

The recruitment of the participants started in December 2023, and the final follow-up was completed in April 2024. Out of the total 760 enrolled participants, 686 (95.3%) completed the study up to the last follow-up. The study findings will be disseminated in peer-reviewed journals after the completion of data analysis.

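### The withdrawal rule makes possible effects of treatment a way out of the study, and the repeated-measures tests named for the primary outcome use only participants with every visit, so the OPQOL-Brief comparison could be biased

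*Protocol article*

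**What the plan says.** Withdrawal Criteria gives four grounds. Two concern health: "Study participants who developed any serious adverse events, developed any condition mentioned in the exclusion criteria during the study period". The other two are non-compliance and unwillingness; the sentence ends by saying that such participants "were not compliant with the protocol or not willing to continue in the study were free to withdraw from the study". What they may leave is the study, not only the treatment, and no further outcome collection is described. Reasons are kept on file: "Detailed justification for withdrawal of the participant were prepared, indicating the line of further management, if required".

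The exclusion conditions that become withdrawal grounds include "elevated liver enzymes (aspartate transferase and/or alanine transaminase >2 times of the upper normal limit") and a creatinine limit. Outcome Measures lists among the secondary outcomes "hematological and biochemical parameters (complete blood count, liver function test, and renal function test"), at baseline and day 90.

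The primary outcome, the OPQOL-Brief, is measured at baseline and on days 34, 62 and 90. For such outcomes, Statistical Analysis says: "The assessment parameters assigned in more than 2 follow-ups will be analyzed using the r-ANOVA, Friedman test, or Cochran" Q. The between-group tests for continuous variables are the unpaired t test or Mann-Whitney U test. The Blinding section confirms that the trial is open label.

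**The concern.** Of the four grounds, only unwillingness is purely a matter of consent. The other three arise after allocation and can result from treatment. Because everyone knows the allocation, the rate of leaving, and the kind of person who leaves, can differ between arms.

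The named repeated-measures tests add to this. Classical r-ANOVA and the Friedman test need a score at every visit. A participant who leaves after day 62 has three of four OPQOL-Brief scores, and unless values are imputed all three are lost. If those who leave did worse than those who stay, and leave more often from one arm, the analysed groups are no longer the groups that were allocated. The estimated benefit could then be too large or too small.

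**Working it through.** **Inputs.** Planned changes of 9 and 6 points, SD 8, 150 per group before inflation, 360 per group after (Sample Size). 686 of 720 completed, 95.3% (Abstract). The split of losses by arm and the leavers' outcomes are not given, so both are assumed below.

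**The plan's own figures.**
- Planned difference: 9 − 6 = 3.0. The usual two-sample formula with SD 8, two-sided 5% and 90% power gives 150 per group, as stated.
- Completion: 686/720 = 95.3%, as stated. Losses: 720 − 686 = 34, or 4.7%.

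**Formula.** Let n = 360 per arm, k and m the losses in the intervention and control arms, and t and c the leavers' mean changes. If completers show the planned changes, the difference over everyone allocated is

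[9(n − k) + t·k]/n − [6(n − m) + c·m]/n

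**Results with 34 lost.**

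| Split (intervention / control) | Leavers' change | Calculation | Difference |
|---|---|---|---|
| 17 / 17 | 0 | 9·343/360 − 6·343/360 | 2.86 |
| 25.5 / 8.5 (75%) | 0 | 9·334.5/360 − 6·351.5/360 | 2.50 |
| 34 / 0 | 0 | 9·326/360 − 6 | 2.15 |
| 25.5 / 8.5 (75%) | 6 | (9·334.5 + 6·25.5)/360 − 6 | 2.79 |
| 34 / 0 | 6 | (9·326 + 6·34)/360 − 6 | 2.72 |
| 0 / 34 | 0 | 9 − 6·326/360 | 3.57 |

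The last row shows that the direction is not fixed: if the losses were all controls, a completer analysis would understate the difference.

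**Relative size.** Balanced loss with no change costs (3.0 − 2.86)/3.0, about 5%. The one-sided extreme costs (3.0 − 2.15)/3.0 = 28%.

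**What would remove the effect.** With all 34 losses in one arm, the missing fraction is 34/360 = 9.4%. Cancelling 3.0 points would need leavers to differ from completers by 3.0/0.0944 = 31.8 points, about 4 SD. The losses reported could shrink the planned effect but could not plausibly abolish it.

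**A caveat on the count.** The 686 are those who reached the last follow-up. Anyone among them who missed day 34 or day 62 would also drop out of a classical r-ANOVA, so 34 is the least that such an analysis would lose.

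**The case against.** The strongest reply is that the article nowhere states a completers-only analysis. It defines no analysis set and no missing-data rule, and both may properly sit in a full protocol or SAP that is not shown. That stands: dropping incomplete participants is how the named repeated-measures tests work in standard form, not a declared policy. The unpaired between-group test needs only the value being compared, not the full series. The withdrawal wording is also permissive, since participants are free to leave and nobody is ordered out.

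A reader might infer three stronger points that the documents do not support.

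- **That adverse events disappear from the tolerability result.** Outcome Measures counts treatment-emergent events over the study period, and Data Collection records symptoms at follow-ups. An event that precedes withdrawal therefore need not be lost. Liver and renal tests are scheduled only at baseline and day 90, so a breach found on schedule would normally be the day-90 outcome itself. What remains is narrower: an earlier leaver has no scheduled post-treatment laboratory value, and a breach found on an unscheduled test should be reported.
- **That losses fall mainly in the intervention arm.** Only that arm receives the coded drugs, but the criterion is compliance with the protocol, and both arms receive ancillary treatment for 90 days. No losses by arm are given.
- **That more than half the effect is at stake.** Results says: "Out of the total 760 enrolled participants, 686 (95.3%) completed the study up to the last follow-up". Taking 760 gives 74 losses and, in the one-sided extreme, 9·306/380 − 6 = 1.25, a fall of 58%. But 686/760 is 90.3%, not 95.3%, and Table 2 totals 340 + 380 = 720. The 760 is a discrepancy to reconcile, not a basis for a bound.

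**Conclusion.** The point holds in limited form. The withdrawal rule merges stopping treatment with leaving the study, on grounds that treatment can cause. The tests named for multi-visit outcomes discard participants with a missing visit unless something unstated prevents it. In an open-label trial this could bias the OPQOL-Brief comparison; it is not shown to have done so.

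The planned 3.0-point difference becomes about 2.86 with balanced losses and 2.15 at the one-sided extreme, both with no change in leavers. These figures assume 720 enrolled, 34 lost and completers behaving as planned; leavers who worsened would widen the range. Reported loss of 4.7% is well below the 20% allowed for in Sample Size, so this is a worthwhile correction and not a threat to the trial as a whole.

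**What to change.** Follow-up ended in April 2024, so a rule for continued assessment can no longer recover data. The article describes the analysis as still to be done, and the following can use what was collected:

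1. For the OPQOL-Brief, replace r-ANOVA/Friedman with a likelihood-based mixed model on all available visits, covering every enrolled participant according to the allocated cluster.
2. Report withdrawals by arm, reason and timing; the written justifications should already contain this.
3. Include in the tolerability summary any laboratory value that led to withdrawal, scheduled or not.
4. Add one sensitivity analysis in which withdrawn participants are assigned no improvement.
5. Reconcile the 760 in Results with the 720 given in the Abstract, Sample Size and Table 2.

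The cost is modest extra analysis and possibly a slightly smaller estimate. None of this bears on when treatment should be stopped.

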### Study Setting

The study was conducted as a part of the public health care program, through 17 peripheral institutes under the Central Council for Research in Ayurvedic Sciences (CCRAS), Ministry of Ayush, Government of India. For the Ayurveda Mobile Health Care Programme under Scheduled Caste Sub Plan, areas predominantly dwelled by SC population were selected by 8 institutes located at Agartala, Gwalior, Patna, Chennai, Vijayawada, Jammu, Guwahati. and Bangalore, while for the Tribal Health Care Research Programme under Tribal Sub Plan, areas predominantly dwelled by ST population were identified by 9 institutes located at Cheruthuruthy, Bangalore, Nagpur, Gangtok, Ahmedabad, Bhubaneshwar, Kolkata, Mumbai, and Jammu. The participants were screened through outreach outpatient departments, medical camps, and door-to-door visits.

### Study Intervention

Participants from both groups (intervention and control) were provided with ancillary care through Ayurveda for 90 days. In the intervention group, along with ancillary care, 10 g of *Ayush Rasayana* A in powdered form were administered orally with lukewarm water, once daily after food at bedtime for the first 6 days starting from the day of enrollment, and 1.5 g of *Ayush Rasayana* B were administered orally per day in 2 divided doses (2 capsules of 375 mg each) with lukewarm water, before food for 84 days (from the 7th day onward up to the 90th day of enrollment).

Ancillary care was defined as the care needed by research participants but not necessary to ensure scientific validity, prevent study-related harms, or address study-related injuries [12]. The medicines for ancillary care were procured from Indian Medicines Pharmaceutical Corporation Limited, Ministry of Ayush, Government of India. The dose and duration of ancillary care medicine were decided by the investigator based on the clinical presentations mentioned in the protocol. The study interventions *Ayush Rasayana* A and B were coded Ayurvedic formulations developed by the CCRAS (Table 1). These drugs were manufactured by the Central Ayurveda Research Institute Ayurveda Pharmacy, Jhansi, Uttar Pradesh, India (Figures 1 and 2).

**Table 1 table1:** Ingredients of the intervention (Ayush Rasayana A and B).

Study drug	Ingredients
*Ayush Rasayana* A	Harītakī (Terminalia chebula Retz) Sanāya (Cassia angustifolia Vahl) Yashtimadhu (Glycyrrhiza glabra Linnaeus) Rock salt
*Ayush Rasayana* B	Amalaki (Phyllanthus emblica Linnaeus) Asvagandha (Withania somnifera [Linnaeus] Dunal) Gudūcī (Tinospora sinensis [Loureiro] Merrill)

**Figure 1 figure1:**
[figure not shown]
Image of the study intervention: Ayush Rasayana A, procured from the manufacturer.

**Figure 2 figure2:**
[figure not shown]
Image of the study intervention: Ayush Rasayana B, procured from the manufacturer.

### Outcome Measures

The primary outcome measure was the change in the QOL of the older adults, assessed by Older People’s Quality of Life Questionnaire-Brief (OPQOL-BRIEF) at baseline and on the 34th day, 62nd day, and 90th day. The secondary outcome measures included any change in the Katz Index of Activities of Daily Living, Pittsburgh Sleep Quality Index (PSQI), Five Times Sit-to-Stand Test, shoulder joint mobility, hematological and biochemical parameters (complete blood count, liver function test, and renal function test), and the occurrence of treatment-emergent adverse events during the study period at the baseline and on the 90th day.

The OPQOL-Brief is a short measurement for QOL developed from the OPQOL-35 questionnaire [13]. It contains 13 questions scored from 1 (strongly agree) to 5 (strongly disagree) based on the response from the participant. The total score is calculated after reverse coding the positive items so that higher scores represent higher QOL. The Katz Index of Activities of Daily Living is a dichotomous scoring tool used for measuring independence in older adults. It measures the functional independence of a person, assessing self-care tasks under 6 domains: bathing, dressing, toileting, transferring, continence, and feeding [14]. The PSQI is a widely used scale comprising a combination of Likert-type and open-ended questions in 7 components: subjective sleep quality, sleep latency, sleep duration, sleep efficiency, sleep disturbance, use of sleep medication, and daytime dysfunction—each with scores ranging from 0 to 3. Higher PSQI scores indicate more acute sleep disturbances, thus a lower quality of sleep [15]. The Five Times Sit-to-Stand Test is a measure used to assess functional independence and mobility. It evaluates the time required to stand as rapidly as possible from a sitting posture for 5 repetitions; the shorter the time taken by the person, the better the functional condition [16]. The change in shoulder joint mobility is assessed through simple physical maneuvers for the active range of movements: active abduction, and external and internal rotations. Each maneuver is assessed separately by 3-point scales for the range of mobility (fully able=3, partially able=2, and unable=1) and pain on movement (no pain=1, some pain=2, and lots of pain=3) on both sides. A sum score for all 3 maneuvers on each side is estimated for the range of movement and pain separately.

The schedule of enrollment, administration of study intervention, assessments, and follow-up visits are shown in Figures 3 and 4.

